## Discussion

The present single blinded RCT has been designed to explore potential advantages of OMT in the management of newborns’ pain. Currently, based on a patient-centred need-based approach, this research will be looking at the benefit of OMT rather than the efficacy of a specific technique or a pre-determined protocol. Moreover, it will attempt to confirm the effectiveness of OMT on LOS-shortening using a larger experimental study design and to corroborate the absence of placebo effects in newborns. Furthermore, it will explore potential differences between expert osteopaths and final-year students on the effectiveness of OMT.

To date, no osteopathic trial has been carried out in this field attempting to quantify the benefits of OMT in newborns’ pain using rigorous procedures and ‘gold-standard’ methods for clinical trials. This will be the first concrete experimental trial addressing this outcome. The expected advantages from the present trial will be reduction of pain, shorter LOS and lower neonatal costs in the OMT groups compared to sham and control groups.

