### Randomisation and masking

Patients will be randomly assigned in a 1:1:1 ratio to either the OMT, the sham or the control group (Figure 1). Newborns will be eligible for randomisation from the first day of life. Block randomisation will be performed according to a computer-generated randomisation list using a block size of nine, and stratified by OMT group.

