### Statistical analysis

According to Stevens *et al*. [11] the mean PIPP score for a painful procedure is 12.9 (standard deviation (SD), 3.4) and 6.0 (SD, 2.7) for a non-painful procedure. For a heel stick, the mean score is 10.3 (SD, 4.5) and 6.3 (SD, 3.2) for a simulated handling. However, as there is a lack of clinical trials in complementary medicine and/or manual disciplines, the sample size is computed considering an effect size (f) of 0.30, a statistical power of 0.80 and an α-level equal to 0.05 to produce a sample size of 37 per group. To prevent loss of power, the sample size is increased up to 40 subjects per group (total sample N = 120).

The primary analysis of the present clinical trial will be conducted according to per-protocol principle and intention-to-treat. Missing data will be handled using the last observation carried forward imputation technique. Arithmetic means and SD as well as median, percentage and range will be used to describe the general characteristics of the study population. Univariate statistical tests, Student’s *t*-test, analysis of variance (ANOVA) and chi square test, will be performed to compare the study groups and control group at the baseline. A linear mixed effect model will be used to evaluate the PIPP score across groups. Data will be analysed within and between the three study groups. Furthermore, a linear regression model will be applied to study the independent effect of OMT on primary and secondary endpoints between OMT groups A and B. Two-tailed *P*-values of less than 0.05 are considered to indicate statistical difference. To describe imbalances between groups, mean or relative risk with 95% CI will be used. Effect sizes will be computed stratifying by gestational age. R statistical programme (Vienna, Austria) will be used for data analysis [24].

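### The article hopes to confirm that newborns show no placebo effect, but a sham-versus-control difference test with 40 infants per arm cannot support that conclusion

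*Protocol article*

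**What the plan says.** The Discussion sets out what the trial will attempt beyond its main purpose, and includes "to corroborate the absence of placebo effects in newborns". The Osteopathic procedure section defines the two arms that could speak to this. Sham infants get 30 minutes of soft touch with routine care; controls get routine care alone.

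The Statistical analysis section gives the inferential tools. On the model: "A linear mixed effect model will be used to evaluate the PIPP score across groups". Data are to be analysed within and between the three groups. On the decision rule: "Two-tailed *P*-values of less than 0.05 are considered to indicate statistical difference". The sample size rests on "an effect size (f) of 0.30, a statistical power of 0.80 and an α-level equal to 0.05", said "to produce a sample size of 37 per group", then raised to 40 per group and 120 in total. Under Randomisation and masking, allocation is 1:1:1.

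The article attaches no equivalence hypothesis, margin or confidence-interval criterion to the placebo statement.

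**The concern.** The stated aim is a conclusion of no difference. The stated rule can only declare a difference, and the sample size was chosen to detect one. Within the article, the only result that could be offered in support of the aim is a non-significant sham-versus-control comparison. Such a result is expected often even when soft touch has a real, moderate effect.

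The sham arm is there to separate what is specific to osteopathic treatment from the effect of touch and attention. If non-significance were taken to mean that touch and attention do nothing, the treatment-versus-control difference would look wholly specific when part of it might not be. The question is how uninformative a non-significant result would be with 40 per arm.

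**Working it through.** **Inputs from the article (Statistical analysis; Randomisation and masking).** Three groups, f = 0.30, power 0.80, α = 0.05 two-tailed, 37 per group raised to 40, ratio 1:1:1. PIPP SDs cited for single scores: 3.4 (painful procedure), 2.7 (non-painful procedure), 4.5 (heel stick), 3.2 (simulated handling).

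**Assumptions.** The article gives neither the SD of the discharge-minus-entry change score nor an equivalence margin. Effects and margins are therefore shown in SD units over a range. PIPP points are shown only for a change-score SD between 2.7 and 4.5.

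**1. The plan's own figure.** One-way ANOVA F test, k = 3, noncentrality λ = N·f².

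- 37 per group: λ = 111 × 0.09 = 9.99, power 0.803.
- 36 per group: λ = 108 × 0.09 = 9.72, power 0.792.
- 40 per group: λ = 120 × 0.09 = 10.8, power 0.836.

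The stated 37 reproduces. If one arm differs from two equal arms, f = 0.30 corresponds to d = 3f/√2 = 0.64 SD, so the trial is sized for differences of about that order.

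**2. Sham versus control as a difference test.** Two-sample t test, n = 40 per arm, 78 degrees of freedom, noncentrality d·√(n/2) = d × 4.472.

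| True sham effect (SD) | Power | Chance of P>0.05 |
|---|---|---|
| 0.2 | 14% | 86% |
| 0.3 | 26% | 74% |
| 0.4 | 42% | 58% |
| 0.5 | 60% | 40% |

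Power reaches 80% at d = 0.634. If only 37 per arm were analysed, power at 0.3, 0.4 and 0.5 SD would be 25%, 40% and 56%.

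**3. Precision.** 95% half-width = t(0.975, 78)·SD·√(2/40) = 1.991 × 0.2236 × SD = 0.445 SD. In points:

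- SD 2.7: 0.445 × 2.7 = 1.20
- SD 3.2: 1.42
- SD 3.4: 1.51
- SD 4.5: 2.00

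**4. What an equivalence claim would need.** Two one-sided tests at 0.05 each (the 90% interval inside ±m), true difference zero. Approximate n per arm for 80% power = 2·[(z₀.₉₅ + z₀.₉₀)/m]², with m in SD units. Power at 40 per arm was simulated.

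| Margin m (SD) | n per arm for 80% power | Power at 40 per arm |
|---|---|---|
| 0.2 | 429 | about 0% |
| 0.3 | 191 | about 0% |
| 0.4 | 108 | 11% |
| 0.5 | 69 | 43% |
| 0.6 | 48 | 69% |

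Forty per arm gives 80% equivalence power only for a margin wider than about 0.65 SD.

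**The case against.** The strongest reply is that this is one clause in the Discussion. The objectives in Methods/design are pain, then length of stay and cost-effectiveness. The Outcomes section lists one primary and eight secondary outcomes, none of them a placebo hypothesis. To corroborate is also weaker than to prove. All of this is correct and limits the weight of the point. It remains a published purpose of the trial, and the article's own rule and sample size do not support it.

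A second reply is that an analysis plan may exist and may define a margin, and that the mixed model may gain precision. Both are possible. The point is not that a detail is absent; the stated aim does not match the decision rule and sample size that the article does give. A more efficient model would narrow the interval somewhat but would not turn non-significance into evidence of absence.

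Three stronger readings are tempting, and the documents do not support them.

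- **Equivalence within 1 PIPP point is impossible with 120 infants.** No 1-point margin appears in the article, and the change-score SD is not given. The 90% half-width is 1.665 × 0.2236 × SD = 0.372 SD, which falls below 1 point once the SD is under about 2.69. With a true difference of zero, simulated power for a 1-point margin is about 4% at SD 2.7, 11% at 2.5, 43% at 2.0 and 81% at 1.5. Low power over the cited SD range is a fair criticism; impossibility is not.
- **Sham and control will be pooled.** This is planned nowhere; the outcomes and analyses keep three groups.
- **Unit staff are unblinded for this contrast because controls get no session.** The Abstract and the Randomisation and masking section say that staff will not know allocation, and the article does not describe what staff would see during sessions. That is a separate question, and this point does not depend on it.

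**Conclusion.** The concern holds in a limited form. The sample size is arithmetically right for its own purpose, a three-group difference. It does not equip the trial to conclude that sham and control do not differ. A true sham effect of 0.3 SD would give P>0.05 about three times in four, and one of 0.5 SD about two times in five. A non-significant result would leave an interval of about ±0.45 SD around the estimate.

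The SD-unit figures assume a simple two-sample comparison with 40 analysed per arm, without covariates, repeated measures or multiplicity adjustment. The range of 1.2 to 2.0 points also assumes that the change-score SD lies within the cited single-score range.

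A reader might infer that the sponsor has committed to reading P>0.05 as proof of no placebo effect. The article does not say so; it states only what P<0.05 indicates. The finding is that the design supplies no valid route to the stated conclusion. The primary comparison, the sample size and the data collection are unaffected.

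**What to change.** Reword the Discussion aim as: *to estimate the sham-minus-control difference in PIPP change, with its 95% confidence interval*. Add one sentence to the Statistical analysis section saying that P>0.05 for this contrast will not be read as absence of a placebo effect.

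If the sponsor wishes to keep a claim of absence, allow it only when the 90% confidence interval lies wholly within a margin on the PIPP change score. That margin should be justified and fixed in advance, and the equivalence power that 40 per arm gives for it should be reported.

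The cost is two sentences, with no change to arms, procedures or numbers. The sponsor gives up a secondary claim that the design cannot support.

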### Publication policy

The outcomes of the present research will be published in peer-reviewed journals and presented at congresses. The trial will be reported in accordance with the Consolidated Standards of Reporting Trials (CONSORT) recommendations.

## Trial status

The present protocol is for an ongoing research.

## Abbreviations

ANOVA: Analysis of variance
BS: Behavioural state
CONSORT: Consolidated standards of reporting trials
DRG: Diagnosis-related group
GA: Gestational age
LOS: Length of stay
NICU: Neonatal ICU
OMT: Osteopathic manipulative treatment
PIPP: Premature infant pain profile
RCT: Randomised controlled trial
